### Within trial costs and health utilities analysis

Information on the utilization of healthcare services will be obtained from the database of the Independent Sickness Funds. The health care services include primary care visits, visits to emergency departments, visits to specialists, hospital stays, medications, laboratory tests, imaging techniques, paramedical care and other therapies. Out-of-pocket costs will be derived from the published reimbursement regulations. All cost items described above will be specified and expressed in physical, and in monetary units (Euro’s). As baseline measure of costs in both groups, the costs of health care consumption in the 12 months period prior to the trial will be taken. Diabetes – and non-diabetes related costs will be distinguished. Costs imposed by the study that are not part of the routine practice, such as protocol-driven nurse assessment visits and laboratory tests, will not be included into the cost analysis.

The health utility weights will be derived from the Flemish utility value system based on the EQ-5D scores obtained during the assessments visits [30]. QALYs associated with the future diabetes complications will be derived from published sources. QALYs will be calculated assuming linear interpolation between measurement points and calculating the area under the curve, to give a number of QALY gained per patient over the trial period [29].

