### Coaching intervention

The COACH Program consists of 5 monthly telephone sessions of 30 minutes on average delivered by certified diabetes nurse educators (further referred to as “coach”). Prior to the intervention, they undergo 5-days training in up-to date clinical guidelines on diabetes self-management and how to give patients the motivation and the skill to improve their risk factors. Coaches are also trained in the use of the COACH Program software for patient administration. Coaches use patient’s baseline data obtained during the first home visit, to assess the individual risk profile and to suggest targets for diabetes risk factors based on the Flemish and international guidelines for good practice in diabetes care [1,23-25]. The therapeutic goals are discussed with the GP by phone before the first coaching session.

Prior to the beginning of the coaching, patients of the intervention group receive a welcome package with information about the program, a book with advice on nutrition in diabetes and a waist circumference meter with a BMI calculator. Patients with HbA1c above 6% (42 mmol/mol) at baseline, who are not in possession of an insurance-covered meter for self-monitoring of blood glucose (SMBG), receive a SMBG set including lancets and strips.

All risk factors associated with diabetes are addressed by the coaches, - glycaemia, lipids, blood pressure, kidney, foot and eye checks, nutrition, physical activity, smoking and alcohol consumption. Patients are instructed on how to perform SMBG and interpret the results. A measurement frequency of one or two day profiles a week is advised. Depending on the type of the diabetes medication – causing hypoglycemia or not – a scheme of four or two times a day respectively is recommended. Considering special skills needed to assist people in smoking cessation, smokers of the intervention group are motivated to contact the tobaccological service of the Belgian Cancer Federation “Tabakstop” that offers tailor-made telephone sessions and is free for all patients.

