### Data collection and analysis

During the assessment visits, the nurses register data as stated in Table 1. Weight is measured by electronic scale, patients wearing light indoor clothing, no shoes. Height is measured in the standing position using a portable anthropometer, feet, knees, buttocks and shoulder blades in contact with the vertical surface, no shoes. Waist circumference is measured with a measuring tape according to the guidelines of the Belgian Association for the Study of Obesity [26]. Blood pressure is taken in a sitting position by using a manual sphygmomanometer. Two measurements are taken, the lower systolic and diastolic measurements will be used in the analysis. The level of toxic carbon monoxide (CO) is measured in parts per million (ppm) by a CO meter in addition to self-reporting smoking status.

**Table 1 T1:** Patient data collection at three assessment moments during the trial

**Patient data**	**Method of collection**	**Baseline (T0)**	**T0 + 6 months**	**T0 + 18 months**
Gender	Sickness funds database	x		
Age	Sickness funds database	x		
Education	Self-reporting	x		
Occupation	Self-reporting	x		
Diabetes 2 since	Self-reporting	x		
Comorbidities:	Self-reporting	x		x
*Cardiovascular:* CHD; heart failure; atherosclerosis; past MI; stroke; TIA				
*Respiratory:* COPD; asthma				
*Other:* hypoglycemia; hypertension; dyslipidemia; Kidney disease; neuropathy; depression				
Family history of type 2 diabetes and cardiovascular disease	Self-reporting	x		
Blood pressure	Home visit test	x	x	x
Height	Home visit test	x		
Weight	Home visit test	x	x	x
BMI	Calculated	x	x	x
Waist circumference	Home visit test	x	x	x
Prescribed medications	Sickness funds database + self- reporting	x	x	x
Smoking	Self-reporting + CO test	x	x	x
Lifestyle: physical activity; alcohol consumption; healthy eating	Self-reporting	x	x	x
Diabetes risk factor knowledge test	Self-reporting	x	x	x
EQ-5D	Self-reporting	x	x	x
PAID	Self-reporting	x	x	x
DTSQ – status version	Self-reporting	x	x	x
HbA1c	Pathology lab	x	x	x
Lipid profile: TC; HDL; LDL; TG	Pathology lab	x	x	x
Satisfaction about the COACH program (Intervention group)	Self-reporting		x	
Costs	Sickness funds database; time& material sheets; contracts	x	x	x

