### Cost-utility analysis

Cost-utility analysis will be performed if the clinical study demonstrates a positive difference in clinical end points between two study groups [28,29]. Within-trial and modeled cost-utility analyses will be undertaken from the perspective of the health care system, i.e. taking into account direct health care costs to the system including both the cost for the health insurance as the patient out-of pocket costs [30].

The incremental cost-effectiveness ratio (ICER) will be calculated by using the following equation: ICER = ∆Costs/∆QALYs, where ∆Costs is the difference between the mean total cost in the intervention and the control group and ∆QALY is the area between two curves depicting the evolution of the means in QALYs-utilities over time in the intervention and the control group.

Modeling will be applied for projecting effects observed within the trial over a life-time horizon. The assumptions on the progression of type 2 diabetes depending on the known intermediate surrogate outcomes and the associated health status will be derived from published sources. The model’s outcomes validity will be tested through critical appraisal by experts. Future costs of type 2 diabetes without complications, and costs associated with each fatal or non-fatal diabetes-related complication will be estimated based on the epidemiological data available in Belgium and the database of the Independent Sickness Funds. Future costs will be discounted at 3%, future QALYs gained at 1.5% per annum [30]. ICERs will be calculated at various time horizons (e.g., 2, 5, 10, 20 years) [30].

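### Out-of-pocket costs taken only from reimbursement regulations would miss any glucose test strips that patients buy without cover, mainly in the COACH arm

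*Protocol article*

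**What the plan says.** The protocol article's Cost-utility analysis section defines the perspective as that of the health care system, "taking into account direct health care costs to the system including both the cost for the health insurance as the patient out-of pocket costs".

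The section Within trial costs and health utilities analysis then fixes the sources. For resource use: "Information on the utilization of healthcare services will be obtained from the database of the Independent Sickness Funds". For what patients pay: "Out-of-pocket costs will be derived from the published reimbursement regulations". The cost row of Table 1 (Data collection and analysis) lists "Sickness funds database; time& material sheets; contracts". No row of that table records self-monitoring or patients' own purchases.

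Under Coaching intervention, patients in the COACH arm with baseline HbA1c above 6% "who are not in possession of an insurance-covered meter for self-monitoring of blood glucose (SMBG), receive a SMBG set including lancets and strips". The advice that follows is: "A measurement frequency of one or two day profiles a week is advised". Depending on whether the medication can cause hypoglycaemia, "a scheme of four or two times a day respectively is recommended". Set size, resupply and an end date are not stated. Costs of the intervention counts programme materials for patients as a variable cost. The control group receives usual care plus an educational DVD, with no monitoring set and no coaching advice.

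**The concern.** Reimbursement regulations give the patient's share of items that the insurer recognises. An item bought entirely outside cover generates no claim, so it is absent from the fund's database and from any patient share computed by applying the regulations to that database. The programme introduces regular self-monitoring in the patients defined by having no insurance-covered meter, which is where such purchases are most likely.

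At stake is the incremental cost. If intervention patients buy strips because they were advised to monitor, that cost is a consequence of COACH and lies within the stated perspective. Any effect of the monitoring on HbA1c and utility would be counted while part of its cost would not. The ICER would then lean towards COACH, and the lifetime projection would inherit the gap if it assumes that monitoring continues.

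**Working it through.** The plan gives no figure for this item, so there is nothing to reproduce. The check has two parts.

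**1. Can any listed source record a strip bought without cover?**

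| Source | What it captures | Uncovered purchase recorded? |
|---|---|---|
| Sickness fund database | Services and products processed by the insurer | No |
| Published reimbursement regulations | Patient share of reimbursed items | No |
| Time and material sheets, contracts | What the programme spends and supplies | No, but the set itself and any resupply are plausibly captured |
| Table 1 self-report items | Lifestyle, questionnaires, prescribed medications and others | No monitoring or purchase item |

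The exclusion of study-imposed costs does not explain the gap. Its examples are the assessment visits and laboratory tests, whereas self-monitoring is part of COACH.

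**2. How many strips could be involved?**

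Inputs from Coaching intervention: 1 or 2 profile days a week, 2 or 4 tests per profile day. Follow-up is 18 months, about 78 weeks (Study design).

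Advised strips = profile days per week × tests per day × weeks.

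- Per week: 1 × 2 = 2 to 2 × 4 = 8.
- To graduation (26 weeks): 2 × 26 = 52 to 8 × 26 = 208.
- Months 6 to 18 (52 weeks): 104 to 416.
- Full 18 months (78 weeks): 156 to 624.

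Uncosted strips per affected patient = max(0, advised − supplied). The number supplied is not in the document, so the set sizes below are assumptions (no resupply, full adherence):

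| Assumed set | Uncosted if use stops at 26 weeks | Uncosted over 78 weeks |
|---|---|---|
| 25 | 27 to 183 | 131 to 599 |
| 50 | 2 to 158 | 106 to 574 |
| 100 | 0 to 108 | 56 to 524 |
| 200 | 0 to 8 | 0 to 424 |

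The ICER uses the difference in mean cost between arms, so the quantity that matters is an average over the whole intervention arm:

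Missing mean cost = share affected × uncosted strips × price per strip, less the same for strips bought by controls.

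Share and price are also not given. With an assumed share of 30% to 90%, an assumed price of EUR 0.30 to 1.00 and no purchases by controls, the 78-week result runs from EUR 0 (set of 200, lowest frequency) to 0.9 × 599 × 1.00 = EUR 539 per intervention patient (set of 25, highest frequency, full adherence). A range this wide, starting at zero, shows only that the size cannot be settled from the document.

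**The case against.** The strongest reply is that nothing may be missing. The document does not say that patients run out of strips, that they buy more, or that the advice outlasts the five monthly sessions. If the set is generous, or the programme resupplies, the cost is registered as programme material. That these strips are unreimbursed is inferred from the reference to an insurance-covered meter; the regulations are not shown, and a patient who starts insulin becomes entitled to a reimbursed care trajectory. All of this stands, and it limits the size.

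Three stronger readings are tempting and are not supported:

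- *That the omission affects the intervention arm only.* Controls may buy strips too, and some intervention patients may have done so before the trial. Only the net difference biases the ICER, so *mainly* is as far as the text goes.
- *That the cost certainly recurs in the lifetime model.* The article does not say how long monitoring, or its cost, is assumed to last.
- *That a per-QALY bias can be quoted.* For example, 104 to 416 strips a year at EUR 0.50 to 1.00 is EUR 52 to 416, and dividing by an assumed gain of 0.02 QALY gives EUR 2,600 to 20,800 per QALY. That treats every patient as affected and fully adherent, with no strips supplied for that year, and it rests on a single invented QALY gain.

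Two further objections carry less weight. The first is that item-level costing belongs in a fuller document. But this article states its cost sources, and they do not deliver the perspective it states. The second is that one-way, probabilistic and scenario analyses are already planned. They could carry this item, but none names it, and varying the inputs already entered cannot reveal a cost that was never entered.

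**Conclusion.** The point holds as a mismatch between the stated perspective and the stated sources. Any strips bought without insurance cover, beyond what the programme supplies and costs, would not be counted. Because only COACH patients receive the set and the advice, the likely direction is an understated incremental cost and an ICER that favours COACH.

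The direction assumes that the strips are unreimbursed and that intervention patients buy more of them than controls do. The size depends on set size, resupply, duration after graduation, adherence, price and share affected, none of which is given; within the trial it may be nil. The only firm quantity is the advised use of 156 to 624 strips per affected patient over 18 months, if the advice is followed throughout.

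The reach is limited. The cost-utility analysis is run only if the trial shows a positive clinical difference, and the primary HbA1c comparison is untouched. The point still merits correction, because that is the case in which the ICER would inform a reimbursement decision.

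**What to change.** Do not rely on reimbursement regulations alone for out-of-pocket cost.

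1. At assessment visits still to come, ask patients in both arms how many strips and lancets they bought themselves since the previous visit, and value these at retail price. Asking both arms gives the net difference. Recruitment ran from April 2012 to June 2013, so 6-month visits began around October 2012 and some can no longer be covered prospectively.
2. Where purchases were not recorded, add a sensitivity scenario to the within-trial and modelled ICERs. Let use range from zero to the advised frequency, subtract the strips supplied by the programme, and multiply by the observed share of intervention patients without an insurance-covered meter. Keep this as a scenario: imputing full adherence in the base case for intervention patients, and nothing for controls, would bias the ICER against COACH.
3. In the model, apply the cost for as long as continued monitoring is assumed, and state that duration.
4. Report set size and any resupply, so that a reader can see how much use the programme already covers.

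The cost is one question at visits already scheduled and one scenario line in the model. The downsides are recall error and a possibly less favourable ICER. Nothing in the patients' care or in the coaching advice changes.

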### Statistical analysis

The two-tailed unpaired t-test will be used for continuous data and chi-square test for proportions. Where appropriate, regression analysis will be applied to account for baseline differences between the two study groups. The results will be expressed as mean (95% CI) for normal data and median (range) for skewed data. Sensitivity analysis will examine the effect of loss to follow-up on the intervention effect. The analysis will be conducted by intention to treat, which means, all patients will be followed for the full duration of the trial. Exploratory analyses will examine the effect of other factors, such as socio-demographic variables, on the outcome.

ICERs will be calculated for the mean and for the upper and lower confidence levels of marginal costs and utilities. One-way sensitivity analysis will be performed to test the relative contribution of different variables to the uncertainty around ICER and presented by means of a Tornado diagram. Probabilistic sensitivity analysis (Monte Carlo simulation) will be performed for all model inputs. The structural uncertainty will be tested through presenting different model scenarios. The results of this analysis will be presented on the cost-effectiveness plane. Probability of willingness to pay by the Belgian Health Care system will be forecasted and presented as a cost-effectiveness acceptability curve [30].

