## Methods/Design

### Study design

The study is a parallel-group RCT, in which patients with type 2 diabetes, affiliated to the Belgian sickness fund Partena, were selected based on their medication consumption data, recruited by their sickness fund, and randomized to receive usual care plus The COACH Program or the usual care alone. The study will assess the difference in outcomes between the two groups. The primary outcome measure is the level of glycohemoglobin HbA1c at 6 months after randomization. The secondary outcomes are: total cholesterol (TC), low-density lipoprotein (LDL), high-density lipoprotein (HDL), triglycerides (TG), blood pressure (BP), Body Mass Index (BMI), smoking status; proportion of people at target for HbA1c, LDL-Cholesterol and Blood Pressure; self-perceived health status, diabetes-specific emotional distress, and satisfaction with diabetes care. The follow-up period is 18 months. All outcome measurements will be collected 3 times: before randomization, upon the graduation from the program (6 months after the program start); and at the end of the follow-up period (18 months after randomization). The allocation ratio is 1:1. Within-trial and modeled cost-utility analyses, - to project effects over a longer time horizon beyond the trial duration, - will be undertaken from the perspective of the health care system if the intervention is effective.

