### Patient recruitment and randomization

Patients were selected from the administrative database of the sickness fund “Partena” which belongs to the Group of the Independent Sickness Funds, based on the reimbursement data of glycaemia lowering medications in the past 12 months. Prior to the start of patient recruitment, their GP’s were informed about the study by mail. Selected patients were sent a letter of invitation to participate in the study and invited to express their interest by returning an attached response card. Those candidates who expressed their interest, or have not reacted to the invitation within two weeks, were contacted by phone. A home visit for the baseline assessment was scheduled with those patients who confirmed their participation. The assessment visit was carried out by a nurse not involved in the intervention delivery.

Randomization was performed every 2 weeks on average. To achieve a comparable HbA1c distribution within both groups, patients were stratified based on the baseline level of HbA1c: with HbA1c < 7% (53 mmol/mol), or with HbA1c ≥ 7%. Patients from both strata’s were allocated to the intervention or the control group by a data analyst of the Independent Sickness Funds, further not involved into the study, by using a random number generator programmed in Excel.

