### Sample size

Sample size calculation was performed by using the stata software. For the subgroup of people with HbA1c ≥ 7%: assuming the difference of 0.4% between the control and intervention group (7.8% vs 7.4%) [4] and the standard deviation of 0.94% as observed within this subgroup at the baseline data analysis, we would need 232 people in both arms to achieve a power of 0.90 in this subgroup. 46% of the participants represent this group. This means that recruiting 555 people in total would be enough to power our hypothesis for the subgroup of people with HbA1c ≥ 7% at baseline if accounting for up to 10% drop-out.

For the total study population: based on the assumption that the mean difference in HbA1c between two groups will be of 0.3% (7.0% vs 6.7%) [2], and standard deviation of 1.05% - as analyzed at baseline – to achieve a power of 0.90 with alpha being 0.05, we would require 514 subjects to complete the study. Allowing for a dropout rate of up to 10%, the target recruitment number should be 566 patients totally, or 283 patients in each arm [27].

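### Baseline HbA1c is measured in everyone and stratifies the randomisation, yet the default primary test is an unadjusted t-test with discretionary regression; one pre-named ANCOVA would be more precise at no cost

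*Protocol article*

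**What the plan says.** Study design defines the endpoint: "The primary outcome measure is the level of glycohemoglobin HbA1c at 6 months after randomization". It also has every outcome measured before randomisation, and Table 1 confirms HbA1c at baseline, 6 months and 18 months.

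Patient recruitment and randomization says that "patients were stratified based on the baseline level of HbA1c", with the cut at 7%, in order to make the HbA1c distribution comparable between arms.

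Statistical analysis sets the default: "The two-tailed unpaired t-test will be used for continuous data and chi-square test for proportions". The next sentence adds: "Where appropriate, regression analysis will be applied to account for baseline differences between the two study groups". No separate model is named for the primary outcome, so these two sentences govern it. They name no covariates, do not say when adjustment is appropriate, and do not say which result decides.

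Sample size uses a "standard deviation of 1.05% - as analyzed at baseline". That is the unadjusted SD, which is consistent with a plain t-test.

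**The concern.** The design uses baseline HbA1c to balance the arms, but the default analysis does not use it. This has two consequences.

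**Precision.** Baseline HbA1c would normally be expected to predict HbA1c six months later. A t-test leaves that predictable variation in the standard error. It also counts the between-stratum variation that stratified allocation has already removed from the treatment comparison. The interval is therefore wider than necessary, and the test rejects a true null hypothesis less often than 5% of the time.

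**Pre-specification.** The text permits two analyses of the primary outcome and does not rank them. Table 2 already shows small differences between the arms (for example healthy diet 63% versus 55%, smokers 14% versus 19%), so the covariate set is open as well. Under Cost-utility analysis, the economic evaluation goes ahead only if the clinical result is positive, so it should be clear which analysis settles that.

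**Working it through.** **Inputs from the article.** Difference 0.3%, SD 1.05%, alpha 0.05, power 0.90, 514 completers (Sample size). Allocation 1:1 (Study design). Two-tailed test (Statistical analysis). Patients below 7% at baseline: 155 and 159 of 287 per arm, hence 132 and 128 at or above 7%; mean HbA1c 7.0% overall, and 7.9% and 7.8% in the upper stratum (Table 2).

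**Assumption.** The correlation r between baseline and 6-month HbA1c is not in the article. I take 0.3 to 0.8, and assume that the SD at 6 months is also 1.05%.

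**Step 1: reproduce the plan's figure.** n per arm = 2 × (1.960 + 1.282)² × 1.05² / 0.3² = 257.4, so 258 per arm and 516 in total, against 514 stated. Power at 257 per arm is 89.95%. The sample size is sound for the t-test.

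**Step 2: gain from adjustment.** Residual SD = 1.05 × √(1 − r²). The unadjusted standard error at 257 per arm is 1.05 × √(2/257) = 0.0926, and adjustment multiplies it by √(1 − r²).

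| | Unadjusted | r=0.3 | r=0.5 | r=0.7 | r=0.8 |
|---|---|---|---|---|---|
| Residual SD (%) | 1.05 | 1.00 | 0.91 | 0.75 | 0.63 |
| SE relative to t-test | 100% | 95% | 87% | 71% | 60% |
| 95% CI half-width (1.96 × SE) | 0.18 | 0.17 | 0.16 | 0.13 | 0.11 |
| Power for 0.3%, 514 completers | 90.0% | 92.4% | 96.3% | 99.5% | >99.9% |
| Completers for 90% power | 516 | 470 | 388 | 264 | 186 |

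**Step 3: how conservative the t-test is.** Share in the upper stratum: w = 260/574 = 0.453 from Table 2, or 0.46 from Sample size. With an upper-stratum mean of 7.85% and an overall mean of 7.0%, the lower-stratum mean is 6.30% or 6.28%. The stratum's share of baseline variance is w(1 − w)(7.85 − lower mean)² / 1.05² = 0.54 to 0.56. With strata balanced between the arms, the t-test's actual two-sided error is about 2Φ(−1.96/√(1 − 0.555 r²)):

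- r=0.3: 4.4%
- r=0.5: 3.5%
- r=0.7: 2.2%
- r=0.8: 1.5%

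**Step 4: simulation.** 10,000 null trials per value of r, with 514 patients, exact balance within strata and normally distributed baseline values. The Monte Carlo error near 5% is about 0.2 points. ANCOVA here adjusts for continuous baseline HbA1c only.

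| Type I error | r=0.3 | r=0.5 | r=0.7 |
|---|---|---|---|
| t-test | 4.3% | 3.2% | 1.9% |
| ANCOVA | 4.8% | 5.0% | 5.0% |
| Smaller of the two p-values | 5.4% | 5.6% | 5.6% |
| ANCOVA only if baseline HbA1c differs at p<0.05, else t-test | 4.3% | 3.2% | 1.8% |

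The simulated t-test figures agree closely with step 3.

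**Step 5: power under stratified allocation.** Step 2 takes the t-test's power from the usual formula, which ignores the stratification. In 2,000 simulated trials per r with a true 0.3% difference, the t-test reached 91.0%, 91.8% and 94.1% (r=0.3, 0.5, 0.7), against 92.3%, 96.3% and 99.6% for ANCOVA. Stratification alone thus recovers part of the gain; the rest needs the covariate.

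**The case against.** The t-test is a valid analysis of a randomised trial, and here it errs on the safe side. The sample size was computed for it and reproduces. With 574 patients enrolled, a 10% loss leaves about 517, so the planned 514 completers are within reach. At r=0.3 the gain from adjustment is small. An article condenses its protocol, and covariates and triggers may be set out in an analysis plan that is not shown. All of this stands, and it limits the weight of the point.

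It does not remove the point. The article is not merely silent: it states a default test, and a later plan that named ANCOVA as primary would replace that rule rather than fill it in.

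Three stronger readings are tempting but unsupported.

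- **That the trial is underpowered or the t-test wrong.** Steps 1 and 3 show planned power for 0.3% and an error rate below 5%. A more striking power gain can be shown by supposing a smaller true effect, but the article plans for no smaller one.
- **That the analysis will be picked after outcomes are seen.** The text ties regression to differences at baseline, not to outcomes. It leaves the rule unstated, which is a lesser fault.
- **That the choice seriously inflates false positives.** Always taking the smaller p-value gives 5.4–5.6%. A literal rule of adjusting only when baseline HbA1c differs significantly gives no inflation. A freely chosen covariate set could add to this, but nothing in the article shows that one is intended.

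On triglycerides (baseline range 35–1993 mg/dl in Table 2), the section does provide for medians and ranges when data are skewed, but it names no test other than the t-test for them. That is a secondary matter.

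**Conclusion.** The point holds as a free improvement in precision and pre-specification, not as an error that must be corrected for the trial to be valid. The default analysis of 6-month HbA1c leaves out a covariate that is already collected and already used to stratify. The cost is an interval between about 5% (r=0.3) and 67% (r=0.8, since 1/0.60 = 1.67) wider than ANCOVA would give, and a test run at about 4.3% to 1.5% instead of 5%. Which of two permitted analyses decides is not fixed, though the effect of that on the type I error is modest.

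The sizes rest on the assumed correlation, on an SD at 6 months equal to that at baseline, and on near balance within strata. Table 2 supports the last (155 versus 159, and 132 versus 128), although the article describes only a random number generator and no blocking.

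**What to change.** For the primary outcome, replace the two sentences with one named analysis: ANCOVA of 6-month HbA1c on arm and continuous baseline HbA1c, plus the randomisation stratum, reporting the adjusted difference with its 95% CI. Delete the where-appropriate condition for this outcome and keep the t-test as a supportive analysis. Fix this before 6-month outcomes are compared by arm. If the analysis plan already names such a model, bring the two documents into line.

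Use the same baseline-adjusted form for the other continuous outcomes. As a secondary point, analyse triglycerides on the log scale and report a ratio with its CI.

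The cost is wording only. Baseline HbA1c and stratum are already recorded for every patient; no extra patients, visits or measurements are needed, and the sample size can stand.
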